## Abstract

**Background:**

A growing number of emergency calls are made each year for elderly people who fall. Many of them are not taken to hospital or are rapidly discharged from the Emergency Department (ED). Evidence shows that, with no further support, this vulnerable population is particularly at risk of injuries, dependency and death. This study aims to determine the effectiveness of a comprehensive geriatric assessment and a tailored intervention in the elderly calling on an Emergency Medical Service (EMS) for a fall at home, but not conveyed to the ED or rapidly discharged from it (less than 24 h from hospitalisation), to the time to institutionalisation or death.

**Methods:**

Rising-Dom is a two-arm randomised (ratio 1:1), interventional, multi-centre and open study. Community-dwelling elderly people (≥ 70 years) who call an EMS for a fall at home are recruited. The intervention group receives home visits by a nurse with a comprehensive fall risk assessment and a personalised intervention care plan with a planned follow-up (six nurse home visits and five nurse phone calls). Subjects enrolled in the usual care-control group continue to receive their routine care for the prevention or treatment of diseases. Primary (time to institutionalisation or death) and secondary (unscheduled hospitalisations, additional EMS calls relating to falls, functional decline and quality of life) outcome data will be collected for both groups through five phone calls made by Clinical Research Associates (CRA) blind to the participants’ group during the follow-up period (24-months). Twelve hospital centres in the South-West of France are participating in the study as study sites. The inclusion period started in October 2019 and will end in March 2022. By the end of this period, 1,190 subjects are expected to be enrolled.

**Discussion:**

Studies on elderly home falls have rarely concerned people who were not taken to hospital. The Rising-Dom intervention scheme should enhance understanding of features related to this vulnerable population and investigate the impact of a nurse care at home on delaying death and institutionalisation.

**Trial registration:**

Clinicaltrials.gov identifier: NCT04132544. Registration date: 18/10/2019. Sponsor: University Hospital, Toulouse. https://www.clinicaltrials.gov/ct2/show/NCT04132544?term=rising-dom&draw=2&rank=1

## Background

Falls are the first cause of accidental death in people over 65 and have negative physical, psychological and quality of life consequences [1]. Fall-induced deaths of the elderly are in constant increase, especially in modern societies with aging populations [2–4]. In 2016, approximately 30,000 older adults died because of a fall in the USA [5] and the overall medical spending totalled $50 billion in 2015, making falls one of the most costly health conditions among people 65 and older [6]. In addition, falls increase the risk of institutionalisation and are considered as a strong predictor of nursing home placement [7].

Home falls among elderly living in the community may require Emergency Medical Services (EMS). Studies from different countries have shown that calls for falls count for 8% to 17% of all EMS calls [8–10] with a commonly repeated use of EMS for falls [9, 11].

Although many of these subjects require transport to hospitals for examination and care, EMS data from various countries highlight that 11 to 56% of the elderly who received emergency intervention for a fall were not transported to a medical facility, often because they were not injured or refused transport [12–14]. This population is, however, particularly vulnerable and, according to some studies, half of the elderly who have fallen and called EMS had needed "unscheduled care" the month preceding the call [14, 15].

Falls are usually multifactorial and may be associated with age, impaired mobility, sensory deficits, chronic conditions, medication as well as environmental hazards [16, 17]. Numerous studies have evaluated the association between falls and intrinsic factors (for instance frailty [18], functional status [19], vision [20, 21], nutritional status [22–24], medication [25]) and extrinsic events linked to home environment risk factors (slippery floors, inadequate lighting, unstable furniture, loose rugs and carpets, etc.) [26, 27]. Considering the patient in his/her whole environment is hence a relevant issue in the identification of fall risks and the planning of efficient preventive measures [28, 29].

Few studies have focused on older people who call an EMS for a fall but are not conveyed or are rapidly discharged from ED after transportation [14]. They show that no intervention or specific care is scheduled after EMS intervention and the elderly who fall are often not treated in primary care practice [29, 30]. This population seems, however, to be particularly vulnerable with a high risk of mortality and institutionalisation. Therefore, they represent an interesting target for appropriate interventions [31, 32]. The RISING-DOM project has been designed as an answer to a critical request from our ED department to reduce resource utilisation for fall-related calls in the elderly and implementation of a fall-prevention strategy to decrease fall rates and related injuries.

In the RISING-DOM study, we intend to evaluate the subjects (70 years old and over) in their own environment by an experienced geriatric nurse whenever a fall triggers a call to the EMS (without hospitalisation or with an ED admission less than 24 h). A Personalised Intervention Care Plan (PIP) based on an initial comprehensive geriatric assessment is proposed, with targeted and prioritised actions in collaboration with the participant’s general practitioner (GP), hospital geriatrician and other health professionals if necessary. The PIP is based on the patient's desires and concerns and a maximum of three goals are established in order to increase participant's adherence.

The main purpose of the study is to assess the effect of this intervention on time to institutionalisation or death. Secondly, the impact of the PIP will be assessed regarding the number of institutionalisations or deaths, the number and time to first additional EMS call relating to a fall, the number and time to first unscheduled hospitalisation, the functional dependency level and the quality of life during follow up.

## Methods/Design

### Study design

RISING-DOM is a randomised, multi-centre, open, interventional study comparing two groups (ratio 1:1): an intervention group consisting of subjects for whom a comprehensive geriatric assessment (CGA) with a PIP and a planned follow-up are carried out at home by an experienced geriatric nurse versus a usual care control group of subjects that continue to receive their routine care for the prevention or treatment of diseases.

RISING-DOM was designed (Fig. 1) according to a previous pilot study in which the feasibility regarding recruitment, home visits and adherence to the intervention program were tested (unpublished data). In this pilot study, carried out at our institution in 2015 in Toulouse, France (480,000 inhabitants), about 2,797 calls to an EMS for a fall were registered, among which 87% came from an elderly person aged over 70 years old. About 32% of this population called the EMS again regarding another fall in the next 6 months. Ninety-one elderly people who had fallen (mean age 83.6 years old) have been assessed; among them 43% were frail, 14% pre-frail according to Fried criteria [33] and 43% were dependent. About 58% had cognitive disorders (MMSE ≤ 24) and 49% were at risk of undernutrition (unpublished data).

**Fig. 1 Fig1:**
[figure not shown]
RISING-DOM study design. EMS Emergency medical service, ORU-Occitanie Observatory of Occitanie region, e-CRF electronic Case Report Form, MDTM Multidisciplinary Team Meeting, PIP Personalised Intervention care Plan, CRA Clinical research associate, M0, M2, M4, M6, M9, M12, M15, M18, M21 and M24 match months 0,2, 4, 6, 9, 12, 15, 18 and 24 respectively from the enrolment (t0) until the end of the follow-up period

In order to maximise the representativeness of the sample of elderly people who had fallen (rural and urban areas), Toulouse University Hospital and a representative sample of eleven public hospitals within a distance of 155 kms around Toulouse (mostly rural areas) will participate in this study. The RISING-DOM team of each hospital centre consists of a principal investigator geriatrician, a nurse, a Clinical Research Associate (CRA) and associated investigators. Following an EMS home intervention, the EMS staff should provide the potentially eligible population with an information sheet about the RISING-DOM study. Subjects enrolled in this study are identified using the database of the ED Observatory of the Occitanie region (ORU-Occitanie).

### Inclusion and exclusion criteria and recruitment procedure

During the recruitment phase, the ORU-Occitanie makes available to the CRA and investigators participating in this study (via its secured digital professional platform) a daily read-only listing of subjects over 70 years old who have called the EMS because of a fall issue. Calls are automatically screened according to the following key words: fall, fell, fracture, lift, lifted, lifting, on the ground and slipped.

The CRA of each hospital centre is in charge of selecting subjects in his/her territory and ensures that the selected subjects meet the inclusion and exclusion criteria listed in Table 1. Subjects with cognitive and hearing impairments or other disorders are not excluded if they have close relatives or a legal representative able to give consistent phone information. Subjects can be included in the study regardless of the interventions already underway even if they are related to falls prevention. However, subjects with activities of daily living (ADL) set to 0 are excluded, given that PIP intervention would not be appropriate.

**Table 1 Tab1:** RISING-DOM inclusion and non-inclusion criteria

Inclusion criteria	Exclusion criteria
Age ≥ 70 years	Total dependency (ADL at 0)
Living at home	Entry into a nursing home already scheduled in the next 3 months
Living at maximum 45 min from a hospital centre participating in the study (for logistical reasons)	Subject already enrolled in this study
Intervention of the EMS for a fall at home without there being hospitalisation or with hospitalisation less than 24 h	
Participant (close relatives or legal representative) able to give phone information	
Participant (close relatives or legal representative) has given its consent for participation in the study	
Participant affiliated to a social security scheme	

*EMS* emergency medical service, *ADL* activities of daily living [34]

Each CRA has a nominative account to connect to the ORU-Occitanie platform and can see patient forms with their identity (first name, last name,sex, age), contact details [phone number and identity of the caller (patient, family, other)], place of intervention, date and time of the incident, destination to which the patient was possibly referred to and name and phone number of participant’s GP whenever available and the reason for their calls. In order to check whether the daily ORU-Occitanie forms match the inclusion and non-inclusion criteria, the CRA is in charge of calling each subject and ensuring his/her eligibility to be enrolled in this study. Thereafter, the geriatrician investigator calls back the subject to give all the needed information about the study, obtains his/her oral informed consent and proceeds to his/her randomisation via the RISING-DOM electronic Case Report Form secured website (e-CRF). The actions/interventions planned for each group are detailed in Table 2. RISING-DOM is an open study. The enrolled participants, the investigators and the nurses are informed about the study group allocation after randomisation. However, the CRAs who are in charge of collecting data related to primary and secondary outcomes are not aware of this information in order to maximise data collection objectivity.

**Table 2 Tab2:** Details on planned actions/interventions in the RISING-DOM compared groups

***Intervention group***	***Control—usual care group***
CGA and fall record carried out at home by an experienced geriatric nurse at the first home visit	
PIP proposal discussed beforehand by a MDTM and with the GP to modify potentially reversible factors	
Commented delivery of PIP for the fall prevention and healthy aging and log-book providing throughout the nurse home visit	Standard recommendations of fall prevention and healthy aging and log-book sent by e-mail or a postal consignment
Nurse follow-up for implementing the PIP and ensuring its effective application or reporting the possible blocking points over the 24-month follow-up period (6 visits and 5 phone calls)	
CRA phone calls over the 24-month follow-up period to collect primary and secondary outcomes	CRA phone calls over the 24-month follow-up period to collect primary and secondary outcomes

*CGA* Comprehensive Geriatric Assessment [35], *PIP* Personalised Intervention care Plan, *MDTM* Multidisciplinary Team Meeting, *GP* General Practitioner, *CRA* Clinical Research Associate

### Participants

Subjects enrolled in this study are over 70 years old, have fallen at home and called an EMS of the territories participating in the study during the inclusion period, without being hospitalised or hospitalised for less than 24 h. The subjects living in nursing homes are excluded from this study (Table 1).

The patient’s oral informed consent is required. However, if the patient is not able to correctly understand the information provided and/or to express his/her wishes, the oral consent should be given to the investigator by close relatives or the legal representative.

The inclusion period started in October 2019 and lasts 30 months. By the end of this period, a total of 1,190 subjects should be enrolled.

### Data collection procedure and randomisation

During the phone call, prior to the enrolment of each participant, the investigator collects information related to the patient’s medical history, his/her current list of pharmacological and non-pharmacological treatment, his/her lifestyle and previous history of falls.

After study recruitment and collection of baseline data, each participant is randomly allocated (1:1) to either the intervention or control arm. Blocked randomisation with random block sizes will be performed. The randomisation will be stratified according to lifestyle (living alone versus living with one’s relatives) and the existence or not of a history of a fall in the previous 12 months and the site.

Data on outcomes (death, hospitalisations, institutionalisation and number of additional EMS calls relating to falls) are collected prospectively by the CRA at 6, 12, 18 and 24 months (M6, M12, M18 and M24 respectively) of the patient’s follow-up and then every six months until the end of the study for both groups. The Activities of Daily Living (ADL) [34] and quality of life (EQ-5D-5L) [36, 37] scales are collected by the CRA once a year at inclusion, 12 and 24 months of follow-up. The exhaustive list of the variables collected by the CRA during the RISING-DOM study for all patients (intervention and control group) is summarised in Table 3. For both groups, a log-book is given to the participants to prospectively collect the events occurring during the follow-up period such as falls, hospitalisations and other side effects with their date. This aims to help the CRA collect with precision the occurrence of events. This document is not accessed/collected by the study team and it works simply as a memory aid. Data collected during nurse home visits (six visits) and nurse phone calls (five phone calls) for the “intervention group” are listed in Table 4.

**Table 3 Tab3:** RISING-DOM data and timeline collection and for ‘intervention group’ and ‘usual-care control group

	CRA call	Investing call	CRA calls					
		Enrolment allocation	Baseline assessment	Follow-up assessment				
	-t1	t0	M0	M6	M12	M18	M24	^b^
Screening for eligibility	+	+						

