***Outcome data***								
Death				+	+	+	+	+
Institutionalisation				+	+	+	+	+
Hospitalisations				+	+	+	+	+
Additional EMS calls relating to a fall^a^				+	+	+	+	+
ADL [34]			+		+		+	
EQ-5D-5L [36, 37]			+		+		+	

*GP* General Practitioner, *CRA* clinical research associate, Investing investigator, *ADL* activities of daily living, EQ-5D-5L EuroQol-5 Dimension-5 levels, M0, M6, M12, M18, M24 match months 0, 6, 12, 18 and 24 respectively from the enrolment (t0) till the end of the follow-up period. ^a^additional EMS calls relating to a fall are collected via the Regional Emergency Department Observatory of Occitanie. ^b^Data on death, hospitalisation and institutionalisation and additional EMS calls are collected by the CRA (M6, M12, M18 and M24) and every six months until the end of the follow-up period of the last enrolled subject

**Table 4 Tab4:** Participant data collection timeline throughout calls and visit assessments (continued on next page)

	Nurse Visit 0	Nurse Visit 1	Nurse call 2	Nurse call 3	Nurse Visit 2	Nurse call 4	Nurse Visit 3	Nurse call 5	Nurse Visit 4	Nurse call 6	Nurse Visit 5
	≤ 14 d	≤ 30 d	M2	M4	M6	M9	M12	M15	M18	M21	M24

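### Baseline ADL and EQ-5D-5L are tabulated after allocation, against the text, so the covariate-adjusted analyses may rest on scores given by participants who know their group

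*Protocol article*

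**What the plan says.** **Order in the text.** Data collection procedure and randomisation states: "After study recruitment and collection of baseline data, each participant is randomly allocated (1:1) to either the intervention or control arm". The same section says of ADL and EQ-5D-5L that these "scales are collected by the CRA once a year at inclusion, 12 and 24 months of follow-up". The items it has the investigator collect by phone before enrolment are medical history, treatments, lifestyle and previous falls. Neither scale is among them.

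**Order in Table 3.** The t0 column (investigator call) is headed "Enrolment allocation". The next column, M0, falls under the CRA calls and is headed "Baseline assessment". ADL and EQ-5D-5L are marked at M0, M12 and M24 only. The footnote says no more about timing than that "M0, M6, M12, M18, M24 match months 0, 6, 12, 18 and 24 respectively from the enrolment (t0").

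**Recruitment and disclosure.** Under Inclusion and exclusion criteria and recruitment procedure, the CRA first phones to check eligibility. The investigator then calls back, "obtains his/her oral informed consent and proceeds to his/her randomisation via the RISING-DOM electronic Case Report Form secured website (e-CRF"). Participants, investigators and nurses "are informed about the study group allocation after randomisation". The CRAs who collect outcomes are not told. The same section states that "subjects with activities of daily living (ADL) set to 0 are excluded".

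**Use of the scores.** Primary outcome analysis names age and ADL as confounders in the multivariable sensitivity model. Secondary outcomes analysis adjusts the 24-month ADL and EQ-5D-5L comparisons for the score at inclusion, if appropriate. Statistical methods lists both scales among the characteristics described by arm at inclusion.

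**The concern.** A baseline covariate is safe to adjust for because allocation cannot have influenced it. A score taken after a participant has learnt the group lacks that protection. Someone promised two years of nurse visits may rate health or independence differently from someone sent standard recommendations. EQ-5D-5L, with its 0 to 100 scale, is self-rated, and both scales are collected by phone, from a relative where the participant cannot answer. Adjusting for such a score can shift the estimated effect instead of sharpening it.

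A second, smaller consequence is that anyone who dies, withdraws or cannot be reached between t0 and M0 has no ADL value. Unless missing covariates are handled, that person drops out of the ADL-adjusted model.

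**Working it through.** **1. Sequence of contacts.** The claim concerns the order of procedures, so the check is mainly a comparison of passages.

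| Step | Source | ADL / EQ-5D-5L marked? |
|---|---|---|
| -t1, CRA screening call | Table 3; recruitment procedure | No |
| t0, investigator call: information, consent, randomisation | Table 3; recruitment procedure | No |
| Group disclosed | Recruitment procedure | not applicable |
| M0, CRA call, baseline assessment | Table 3 | **Yes, first mark** |
| M12, M24, CRA calls | Table 3 | Yes |

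The section describes Table 3 as the complete list of what the CRA collects, so the blank cells at -t1 and t0 carry weight. As tabulated, the two scales follow randomisation. The text puts baseline data before it.

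**2. Interval between t0 and M0.** No window is given. Nurse visit 0 is due within 14 days (counted from the EMS intervention in Experimental design, from enrolment in the Table 4 footnote). Nothing shown places M0 before or after that visit.

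**3. Where the scores enter the analysis.**
- Primary log-rank test: not used.
- Adjusted survival model, a sensitivity analysis: ADL is used.
- ADL and EQ-5D-5L at 24 months: the inclusion score is used, if appropriate.
- Baseline description by arm: both are used.

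**4. Sample size, to confirm that it is untouched.** For HR 0.679, two-sided alpha 0.05 and 80% power, Schoenfeld's formula gives 4 × (1.960 + 0.842)² / (ln 0.679)², which is 210 events after rounding up. Freedman's gives 215. The plan states 211, which gives power 0.803. Neither scale enters this calculation.

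**5. How a reporting shift would carry through.** Let d0 be the between-arm shift in the M0 score caused by knowing the group, d24 the same kind of shift at month 24, and b the slope of the 24-month score on the M0 score. Randomisation makes the true baseline difference zero in expectation, so:

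bias of adjusted difference = d24 − b × d0

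The document gives none of the three. With b assumed at 0.5 to 0.7:
- Shift at M0 only (d24 = 0): bias = −0.5 × d0 to −0.7 × d0. Between 50% and 70% of the shift enters with reversed sign, whereas the unadjusted comparison has no bias from this source.
- Same shift at both times (d24 = d0): bias = (1 − b) × d0 = 0.3 × d0 to 0.5 × d0, whereas the unadjusted bias is 1.0 × d0. Here adjustment helps.

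Neither the size nor the sign of the net bias is determined. In the Cox model the log hazard ratio would move by roughly −γ × d0, where γ is the log hazard ratio per ADL point. The document gives no value for γ either.

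**The case against.** **The contradiction may be only apparent.** The baseline data in the quoted sentence could mean just the investigator's items, which Table 3 does mark at t0. M0 is month 0 and could be the same day. This is a possible reading, but it does not remove the point. The M0 column is itself titled as the baseline assessment, Statistical methods counts both scales among the inclusion characteristics, and a same-day call made after t0 still follows randomisation. What stands is that the order is unclear and M0 has not been shown to follow disclosure in practice.

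**The assessor is blind.** This is correct, and it limits assessor bias. It does not blind the person answering. That a relative answering as proxy also knows the group is an inference, since the article mentions only participants, investigators and nurses.

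**Windows and missing covariates belong in the full protocol or the analysis plan.** This is fair, and the missing M0 window is not a fault by itself. The fault is that the article states one order and tabulates another.

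**Stronger readings that the document does not support:**
- *A reader might infer that the ADL = 0 exclusion is applied on post-randomisation data.* It is not. The CRA checks eligibility by phone before the investigator's call, and Table 3 marks eligibility screening at -t1 and t0. All that can be said is that no recorded ADL score is listed at that stage. Other criteria, such as travel time to a centre, have no row of their own either.
- *A reader might infer that the primary result is at risk.* The primary analysis is an unadjusted log-rank test that uses neither score.
- *A reader might infer that M0 is contaminated by the intervention.* No passage places M0 after nurse visit 0. That visit is the assessment, and the care plan is delivered at the following one.

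**Conclusion.** The point holds in a limited form. Text and table disagree on whether baseline ADL and EQ-5D-5L precede allocation. If the table is followed, the adjusted sensitivity model for the primary outcome and the baseline-adjusted models for the two scales may condition on values reported with knowledge of the group.

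The primary log-rank test, the 211 events and the 1,190 subjects stand unchanged. The size of any bias is unknown. The 50% to 70% pass-through rests on an assumed slope and on a shift present at M0 but not at month 24. If the shift persists, adjustment removes part of it. The number of subjects who would lack an M0 score is also not given.

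The matter deserves correction because it is cheap to settle and these scores feed pre-specified analyses. It does not threaten the trial's main conclusion.

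**What to change.** 1. **Reconcile the text and Table 3.** Collect ADL and EQ-5D-5L after consent and before randomisation, or at least before the group is disclosed, and have the e-CRF refuse randomisation until both are entered. Moving them to the -t1 call is not suitable, because that call precedes the information and consent given by the investigator. *Cost:* an e-CRF setting and a slightly longer or re-ordered enrolment call.
2. **Subjects already enrolled.** Report the M0 date relative to t0 and to disclosure, by arm, with the number lacking an M0 score.
3. **Analysis.** Make the main adjusted survival model the one using covariates recorded before randomisation: age, living situation, fall history and site. Show the ADL-adjusted model as supportive where M0 followed allocation. For the ADL and EQ-5D-5L outcomes, say whether the inclusion score preceded allocation. If it did not, justify its use and show the result without it. *Cost:* some precision may be lost without the baseline score. Statistical methods allows analysis-plan changes before database freeze with the Scientific Council's approval.
4. **Screening record.** State how the ADL = 0 criterion is recorded at screening. *Cost:* one line.

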***Sociodemographic & medical data***								
Date of birth	+							
Sex	+							
Participant personal data	+							
GP information data	+							
Date, hour and location of fall	+							
Fall circumstances and consequences	+							
Legal protection measures	+							
Education level	+		+					
Life style (living alone or with a partner, family, etc.)		+						
Domestic aid			+					
Medical history		+						
Fall history in the last 12 months		+						
Medical and non-medical treatments		+						
Number of hospitalisations in the last 6 months			+					

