### Primary outcome analysis

For the primary outcome, an intention to treat analysis will be conducted and will compare time to institutionalisation or death (before institutionalisation) between the two groups using a two-sided log-rank test in accordance with the sample size of the study. The subjects will be censored in case of an event occurrence or loss to follow-up. A sensitivity analysis will be conducted by a multi-variable survival model (with a Cox proportional-hazards model in the event that the risk proportionality hypothesis is verified) in order to take into account the stratification parameters and potential identified confounding factors (i.e. age and ADL). Marginal models with a robust variance–covariance matrix or sandwich estimator will be considered. Additional sensitivity analyses will be conducted taking into account the subjects who have been institutionalised (*i.e.* people placed in a nursing home) or who have already died at the time of their missed follow-up. The raw and adjusted hazard ratios will be expressed with their confidence interval set at 95%.

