### Secondary outcomes analysis

The analysis of the secondary outcomes are conducted according to *(i)* a similar approach to that described for the analysis of the primary outcome for the criteria: time to the first additional EMS call relating to a fall and time to the first unscheduled hospitalisation *(ii)* the mean number of EMS calls relating to a fall, the mean number of unscheduled hospitalisations and the percentage of deceased or institutionalised subjects at 24 months will be compared between the two groups by generalised linear multi-variable models adjusted on the stratification and the potential confounding factors (age and AD, in particular) *(iii)* the comparison between the two groups of the level of the functional autonomy (ADL scale) and the quality of life ( EQ-5D-5L scale) at 24 months will be carried out by generalised multi-variable linear models adjusted to stratification and to the potential identified confounding factors (age) and the level of the score (ADL or EQ-5D-5L at inclusion) if appropriate.

Additional per protocol analysis will be conducted in the population of subjects who have complied with the protocol (in the intervention arm having accepted at least 80% of all visits and calls proposed during follow-up and for whom a PIP will have been proposed).

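### The EMS-call count model uses past falls only as a yes/no stratum; a prespecified pre-randomisation count would be a cheap, modest gain in precision for this secondary outcome

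*Protocol article*

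**What the plan says.** Under Data collection procedure and randomisation, allocation is stratified by living alone or not, and by "the existence or not of a history of a fall in the previous 12 months and the site". The fall-history stratum is therefore binary.

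Under Secondary outcomes analysis, item (ii), the number of fall-related EMS calls is compared by "generalised linear multi-variable models adjusted on the stratification and the potential confounding factors (age and AD, in particular"; AD is evidently a slip for ADL. Item (i) gives the time-to-event version "a similar approach to that described for the analysis of the primary outcome for the criteria: time to the first additional EMS call". That approach, under Primary outcome analysis, is a comparison "using a two-sided log-rank test in accordance with the sample size of the study", followed by a multivariable sensitivity model with "stratification parameters and potential identified confounding factors (i.e. age and ADL". No count of earlier falls or earlier EMS calls is named in any of these.

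Item (iii) does adjust ADL and EQ-5D-5L at 24 months for the score at inclusion, where appropriate.

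Among the baseline data, Table 3 lists "Fall history in the last 12 months" at t0 without saying whether it is a number. It also has a baseline count of hospitalisations in the last 6 months, but no row for EMS calls before enrolment.

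**The concern.** Fall-related calling is repetitive in this population. In the pilot, "About 32% of this population called the EMS again regarding another fall in the next 6 months", and the Background and Discussion also describe repeated use. If people differ in how often they call, and the difference lasts, a person's past count predicts the later count. A yes/no indicator captures little of that when most people fall on one side of it.

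The plan already adjusts ADL and EQ-5D-5L for the baseline level of the outcome. The EMS-call count, which answers the Background's stated reason for the project (less resource use for fall-related calls), has no such term.

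At stake is the width of the confidence interval, and so the power, for a secondary outcome. A count fixed before randomisation cannot be affected by allocation, so adding it carries no risk of bias.

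**Working it through.** **The plan's own figure.** No precision or power is stated for EMS calls. The only stated calculation is for the primary outcome, and it reproduces:
- HR = ln(1 - 0.126)/ln(1 - 0.18) = 0.6786, where 0.126 = 0.18 × 0.7.
- Schoenfeld events for 0.679 at 80% power and two-sided 0.05: 4 × (1.960 + 0.842)² / (ln 0.679)² = 210, against the stated 211.

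This does not bear on the EMS-call model.

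**Inputs from the document.** 1,190 participants, 1:1; the EMS-call rate over 24 months; 32% of pilot callers over 70 calling again within 6 months.

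**Assumed inputs, not in the document.** How unequal people are in their tendency to call; how far that tendency persists from the year before to the two years after randomisation (correlation 0.3, 0.6 or 0.9); three falls per EMS call; full 24-month follow-up; age and ADL left out.

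**Method.** Simulate past and future counts from correlated personal rates. Calibrate the mean so that the chance of at least one call in 6 months is 0.32. For negative binomial counts with dispersion k this solves (1 + kλ)^(-1/k) = 0.68, so λ = (0.68^(-k) - 1)/k = 0.43, 0.47 and 0.58 for k = 0.5, 1 and 2. Fit negative binomial models with treatment plus the yes/no term, then add log(1 + prior count). The cut in variance of the log rate ratio is 1 - (SE with count / SE without)².

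**Results, dispersion 0.5 to 2.**

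| Persistence | Prior EMS calls | Prior falls |
|---|---|---|
| 0.3 | about 1% | about 1% |
| 0.6 | 2-3% | 4-5% |
| 0.9 | 5-15% | 12-19% |

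**Results, lognormal tendency, log-scale variance 0.5 / 1.0 / 1.5 (60 replicates each).**

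| Persistence | Prior EMS calls | Prior falls |
|---|---|---|
| 0.3 | 0.5 / 1.1 / 1.7% | 1.2 / 2.0 / 2.3% |
| 0.6 | 2.8 / 5.8 / 8.4% | 6.1 / 10.0 / 12.2% |
| 0.9 | 7.3 / 18.5 / 26.0% | 16.5 / 29.7 / 37.3% |

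The two sets agree in direction and differ in size. The documents cannot decide between them, because a single figure of 32% fixes neither the spread nor the persistence.

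**What it means for power.** Take lognormal variance 1.0 and persistence 0.6, with power Φ(|ln 0.80|/SE - 1.96) for a rate ratio of 0.80:
- yes/no only: SE 0.075, power 84%
- plus prior EMS calls: SE 0.073, power 86%
- plus prior falls: SE 0.071, power 88%

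**How much the stratum does alone.** In the lognormal runs 72-82% of participants were in the yes stratum, and the yes/no term cut the variance by about 0-13% against no adjustment. The 72-82% follows from the assumed ratio of falls to calls; the protocol gives no such prevalence.

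**The case against.** The strongest reply is that the count is unnamed, not excluded. The words in particular leave the count model's covariate list open, and the article says that a detailed analysis plan will follow. That stands, and a reader who infers that the plan has ruled the count out goes too far. The point survives as a recommendation, because an open list does not prespecify anything and a covariate chosen after the data are seen is weaker.

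A reader might also infer that substantial precision is being thrown away almost for free. Neither half is supported.
- **Size.** With perfectly constant tendency and dispersion 2, prior EMS calls would cut the variance by 29-37% and lift power for a 20% lower rate from 77-80% to 91-93%. Nothing in the document supports constancy over three years in a cohort whose pilot mean age was 83.6.
- **Cost.** The recruitment section describes only a daily read-only listing from the ORU-Occitanie platform, with no look-back. Table 3 does not say that fall history is a number.
- **Recall.** The fall count would be recalled by telephone. In the pilot 58% had an MMSE of 24 or below, and proxy information is accepted. The simulated gains from prior falls include no recall error.

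Finally, the covariate does nothing for the main test of time to first EMS call, which is a log-rank test. It can enter only the adjusted sensitivity model, and no gain was calculated for that endpoint.

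**Conclusion.** The point holds as a cheap improvement in precision for a secondary outcome, and no further. As the models are stated, past falls enter only through the binary stratum, while item (iii) uses the baseline value for ADL and EQ-5D-5L.

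The expected cut in the variance of the log rate ratio is roughly 1-5% at weak to moderate persistence and 5-19% at strong persistence. Larger cuts need a nearly constant tendency to call, or the more unequal tendencies of the lognormal runs. All of these figures rest on assumed heterogeneity and persistence, and they lean high because age and ADL, which the plan does adjust for, were not in the simulated models.

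There is no bias, no type I error problem, no contradiction in the protocol and no effect on the primary outcome.

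**What to change.** Before database freeze, and without reference to outcome results by arm, prespecify one extra covariate in the EMS-call count model and in the adjusted sensitivity model for time to first EMS call:
- log(1 + number of falls in the last 12 months, from the t0 call), if that item is recorded as a number; or
- log(1 + number of fall-related EMS calls in the 12 months before the index call), if the ORU-Occitanie platform allows the look-back.

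Choose one for the whole trial according to which is available. Keep the yes/no stratum, age and ADL, and correct AD to ADL. Leave the log-rank test as it is.

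The cost is one line in the analysis plan and the Scientific Council approval that the article already foresees for changes, plus one numeric field or one look-up per participant. The look-up may need a request to the platform, and the fall count carries recall error. If neither count can be had, the stated model can stand.
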